### Sample selection and recruitment

The potential participants are being identified by means of geographical, socioeconomic and clinical stratification processes. A distinction is made between the individual and social dimension of vulnerability, leading to different recruitment strategies that will be combined to be more efficient. First, geographical mapping of areas with a higher percentage of vulnerable population was done based on existing national and local indices in all participating countries. Consecutively, individualised recruitment will take place in these areas employing specifically designed actions. Multiple recruitment channels are used in coordination with local agents from the healthcare system, social services and community-based structures. More specifically, the following profiles and organisations are involved in recruitment: health professionals, pharmacists, social workers, non-governmental organisations, city councils and associations. The recruitment strategy at each study site is adapted to the specific local circumstances and collaborating organisations.

### Stratification

To identify the people who will benefit most from the programme, individual socioeconomic and clinical parameters will be measured by a multidimensional stratification analysis. The tool used for this purpose, the ‘SELFY-MPI’, has been developed based on the validated Multidimensional Prognostic Index.^22^ The new tool is self-administrable and was specifically designed for EFFICHRONIC,^23^ adapting it to the broad adult population (not limited to the elderly) and incorporating the socioeconomic parameters from the Spanish Gijón scale: education, income, cohabitation, age and social support.^24^ Income categories are country-specific and built on the corresponding minimum wages.

### Implementation

Once the target population is identified and recruitment is ongoing, the programme can be implemented. To reach the target sample size of 2000 people, between 100 and 140 workshops (20–28 per country) will have to be conducted. In practice, for about a year and a half, one workshop will start every month at each study site.

### Evaluation

The last phase of the project consists of evaluating the effectiveness of the programme when it comes to changing health-related behaviour, self-efficacy and quality of life. Furthermore, the economic and efficiency impact will be analysed through cost–benefit analyses. An autoadministrable impact questionnaire, containing validated scales and measuring tools, has been designed to assess these different outcome measures at baseline (T0, before the CDSMP) and 6 months (T1).^25^

### Statistical analysis plan

Differences between baseline and follow-up measurements will be assessed employing the paired T-test (for normally distributed variables), the Mann-Whitney U test (for variables not normally distributed) and the Pearson χ^2^ test (for variable fractions). To adjust for multiple testing, one-way analyses of variance with post hoc testing (type Bonferroni) will be performed. The relationship of an outcome measure (T1) with explanatory variables will be determined using ordinary least squares regression analysis. The outcome measure (T0), (change in) other outcome measures, risk factors and social determinants may serve as explanatory variables. Additionally, the above-mentioned analyses will be repeated for each country separately and possibly for other subgroups (for variables which are likely to influence the effect of the intervention itself, eg, age and gender). All data from each of the five pilot sites will be anonymised and centralised at one study site for statistical analysis. Analyses will be performed with SPSS V.25.0.

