### Sample size

The study primarily wishes to demonstrate a statistically significant difference in the two subscales of the 12 items Short Form (SF-12)^20^ measuring health-related quality of life, and in the five participating countries. Based on a study on the effect of the CDSMP in lumbar back pain, the subscores ‘well-being’ and ‘energy’ of the SF-36 improved by 6.0±19.1 and 4.3±23.2, respectively, after 6 months.^21^ The lowest Cohen’s d is therefore of 0.185 in quality of life domains. Thus, the principal conclusion of the study will rely on 10 tests. Applying the Bonferroni’s correction on the significance threshold, we will consider an alpha risk of 0.005 for the tests measuring the quality of life (self-rated with SF-12) in vulnerable patients with chronic diseases and caregivers. To show a statistically significant effect size of 0.185, by a paired Student’s t-test, with a bilateral alpha risk of 0.005, a power of 0.9 and a correlation between baseline and 6 months of 0, we need to analyse 978 subjects. Assuming a drop-out rate of 20%, we need to include at least 1223 subjects. The multicentre study will include 2000 subjects (400 per country), which will bring about sufficient power to analyse the objectives.

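### The SF-12 conclusion is sized on a paired t-test, but the analysis rule can switch those tests to Mann-Whitney U, which ignores the pairing

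*Protocol article*

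**What the plan says.** Two sections of the protocol article bear on this.

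- **Sample size.** The aim is to show "a statistically significant difference in the two subscales of the 12 items Short Form (SF-12") in the five countries. "Thus, the principal conclusion of the study will rely on 10 tests", and the calculation is done "by a paired Student’s t-test, with a bilateral alpha risk of 0.005". No condition on distribution is attached.
- **Statistical analysis plan.** Baseline and follow-up are compared by "the paired T-test (for normally distributed variables), the Mann-Whitney U test (for variables not normally distributed"), with a chi-squared test for proportions. Further on, "the above-mentioned analyses will be repeated for each country separately".

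The second section gives SF-12 no separate treatment. It does not say how normality is judged, or whether on the scores or on the paired changes.

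**The concern.** The test for the principal endpoint is unconditional in one section and depends on the data in the other. Three things follow.

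- A subscale judged non-normal moves to a test for which no sample size was calculated.
- If normality is judged afresh in each country, the same subscale could be tested on mean change in one country and by a rank comparison in another. The ten results would then not answer one question.
- The alternative named is an independent-samples test. Here the same people are measured twice, so it discards the within-person correlation that makes a pre-post design efficient.

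The condition also buys little. With 400 people per country and 2000 overall, the t-test on the mean change does not need normal scores. What it concerns is the distribution of the change, not of the variable.

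**Working it through.** **Inputs from the Sample size section.** Effect 4.3/23.2 = 0.1853; two-sided alpha 0.05/10 = 0.005; power 0.9; correlation r = 0; 400 per country, taken here as analysed.

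**Assumptions made here.** Values of r other than 0; bivariate normal scores for the power comparison; Shapiro-Wilk at 5% as the normality check; gamma-shaped skewed scores.

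**1. The protocol's own figure.** The standardised change is dz = d/√(2(1−r)). At r = 0 this is 0.1853/1.4142 = 0.1311. The normal approximation gives n = ((2.807 + 1.282)/0.1311)² ≈ 973. The exact noncentral t gives 978, and 978/0.8 = 1222.5, so 1223. Both stated figures reproduce, and they belong to the paired t-test.

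**2. Cost of ignoring the pairing, n = 400, d = 0.185, r = 0.5.**

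- Paired t: dz = 0.185/√(2 × 0.5) = 0.185. The expected statistic is 0.185 × √400 = 3.70, and power ≈ Φ(3.70 − 2.807) = Φ(0.89) = 0.81.
- Unpaired comparison: the expected statistic is 0.185 × √(400/2) = 2.616. Its true standard deviation is √(1−r) = 0.707, but the test takes it to be 1. Power ≈ Φ((2.616 − 2.807)/0.707) = Φ(−0.27) = 0.39. Using ranks costs slightly more.

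Simulated power at alpha 0.005 (3000 runs per cell):

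| n | r | Paired t | Mann-Whitney U | Signed-rank |
|---|---|---|---|---|
| 400 | 0 | 0.403 | 0.382 | 0.380 |
| 400 | 0.5 | 0.814 | 0.373 | 0.789 |
| 400 | 0.7 | 0.973 | 0.317 | 0.968 |
| 978 | 0 | 0.902 | 0.879 | 0.886 |
| 978 | 0.5 | 0.998 | 0.949 | 0.998 |

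Repeat runs of the Mann-Whitney cell at n = 400 and r = 0.5 gave 0.36 to 0.38. With no true change, n = 400 and r = 0.5, Mann-Whitney U rejected in none of 3000 runs at nominal 0.005, and in 0.7% at nominal 0.05. The error is therefore one of missed effects, not of false positives.

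**3. How often a switch would occur.** Let q be the chance that Shapiro-Wilk rejects at n = 400. If each country is checked separately, one subscale gets mixed tests across five countries with probability 1 − q⁵ − (1−q)⁵.

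| Score skewness | q | Mixed tests |
|---|---|---|
| 0.1 | 0.09 | 1 − 0.000 − 0.624 = 0.38 |
| 0.2 | 0.273 | 1 − 0.002 − 0.203 = 0.80 |
| 0.3 | 0.586 | 1 − 0.069 − 0.012 = 0.92 |
| 0.5 | 0.964 | 1 − 0.833 − 0.000 = 0.17 |

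The answer depends entirely on a skewness that the article does not give.

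**4. If the alternative were a paired rank test.** Suppose the scores have skewness 0.2 to 0.5 and the same shape at both times. The change is then nearly symmetric. The t-test and signed-rank test disagree in about 5 to 8% of samples, and their power at r = 0.5 is within about 0.03. They part only when the change itself is skewed. At n = 400, a mean change of 0.185 SD and change skewness +0.5, power is 0.82 (t) against 0.51 (signed-rank).

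**The case against.** The two sections can be read together. The Sample size section names the paired t-test for SF-12 specifically, while the other section is a general menu for all outcomes. Repeating analyses by country need not mean re-judging normality by country. A condensed article may leave the normality criterion to a fuller plan. Choosing a test by distribution is also common practice, and with a paired rank alternative it would rarely change the result.

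Much of this stands. The missing criterion is not a fault in itself, and different tests in different countries is a possibility, not a stated intention. But the rule is stated, covers all baseline to follow-up differences and does not exempt SF-12, so the conflict is in the text. The defence based on a paired rank test does not apply to the test that the article names.

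A reader might infer that the ten tests will be of mixed type and mostly not the sized one. The documents do not support that. At skewness 0.2, about 73% of country samples would keep the t-test. At 0.5 nearly all would switch, but together, with mixed tests in only about 17% of studies. Both halves are likely only near 0.3, and even that presumes a particular check.

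A reader might also infer that rank testing in itself wrecks the error rate. Rejection of about 12% instead of 0.5% does appear in simulation, but only when the changes have skewness of 1. It also holds the rank test to a zero-mean hypothesis that it does not test.

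**Conclusion.** The concern holds as a conflict about the principal test, made material by the alternative that is named. The ten SF-12 tests may not be the test that was sized and may differ between countries; the frequency cannot be derived.

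Where a switch occurs, the size of the loss depends on the baseline to follow-up correlation. At r = 0, the protocol's own assumption, it is about 0.02 in power. At an assumed r = 0.5 with 400 per country, power falls from about 0.81 to about 0.37, and the gap widens at 0.7. With 978 people the loss is modest (0.95 against 1.00 at r = 0.5), so the harm lies in the country-level tests, on which the principal conclusion rests.

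The power figures assume bivariate normal scores. This should be corrected before analysis, but it does not call the design or the reproduced sample size into question. Whether 400 per country suffices for tests sized at 978 is a separate matter.

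**What to change.** In the Statistical analysis plan section, state that both SF-12 subscales are analysed by the paired t-test on the difference between T0 and T1, overall and in every country, whatever the distribution. Add that the Wilcoxon signed-rank test is a sensitivity analysis only.

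For secondary paired outcomes where a rank test is kept, replace Mann-Whitney U by the Wilcoxon signed-rank test, and judge the distribution on the paired differences, not on the scores.

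The cost is two or three sentences. No extra data, participants or sample size calculation is needed, and the analysis section then agrees with the Sample size section.

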### Study design

EFFICHRONIC is a multicentre non-controlled prospective study with a duration of 3 years in five European settings: the Principality of Asturias in Spain, the area of Genoa in Italy, several regions in the UK, the Occitanic region in France and the area of Rotterdam in the Netherlands. The participating countries represent a wide range of social, economic and healthcare-related realities. The EFFICHRONIC intervention consists of the following phases: identification, recruitment and stratification of participants from vulnerable populations, implementation of the intervention and an economic and efficiency evaluation with a pre–post design. Additionally, guidelines and policy recommendations will be developed based on the project conclusions, this to allow the scaling-up of the intervention to other contexts.

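### Two of the three tests named for the baseline to 6-month comparison assume independent samples, so changes in non-normal and categorical outcomes may be missed, mainly in the per-country analyses

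*Protocol article*

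**What the plan says.** The Study design section describes a single group followed over time: "EFFICHRONIC is a multicentre non-controlled prospective study with a duration of 3 years in five European settings". It evaluates that group "implementation of the intervention and an economic and efficiency evaluation with a pre–post design". The Evaluation section says that one questionnaire is used "to assess these different outcome measures at baseline (T0, before the CDSMP) and 6 months (T1").

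The Statistical analysis plan section then gives one sentence on how change is tested. It opens with "Differences between baseline and follow-up measurements will be assessed employing the paired T-test (for normally distributed variables") and continues with "the Mann-Whitney U test (for variables not normally distributed) and the Pearson" chi-square "test (for variable fractions"). All three tests serve the same purpose, the difference between baseline and follow-up. The section adds that the analyses are repeated within each country.

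The Sample size section treats the comparison as paired. The SF-12 calculation is done "by a paired Student’s t-test, with a bilateral alpha risk of 0.005, a power of 0.9".

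**The concern.** The t-test in that sentence is paired. The other two tests are not: the Mann-Whitney U test and the Pearson chi-square test of two proportions are valid when the two sets of values come from different people. Here each participant supplies both values. The sentence therefore recognises the pairing for normal variables and drops it for all others.

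Ignoring a positive within-person correlation makes the assumed variance of the change too large, so p-values are too large as well. Any outcome that is categorical or judged non-normal would be tested with less power than the data allow. Health-related behaviour is one of the stated evaluation targets and may well include such outcomes. The country results are to inform policy recommendations, so a real change missed in one country could carry through to them.

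**Working it through.** **Inputs.** From the Sample size section: effect size d = 0.185 (4.3/23.2), two-sided alpha 0.005 (0.05/10), power 0.9, planning correlation 0, drop-out 20%, 400 participants per country and 2000 in all. The within-person correlation ρ is not given apart from the planning value of 0, so ρ = 0 to 0.7 is assumed as a range.

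**The plan's own figure.** For a paired comparison, n = 2(1−ρ)(z₁₋α/₂ + z_power)²/d². With ρ = 0 this is 2 × (2.807 + 1.282)²/0.185² = 977. The exact noncentral-t calculation gives 981, and the plan states 978. Dividing 978 by 0.8 gives 1223, as stated. The sample size therefore reproduces and does not depend on this point.

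**Size of an independent-samples test on paired data.** Such a test assumes that the mean difference has variance 2σ²/n. The true variance is 2σ²(1−ρ)/n. The true size is therefore 2[1 − Φ(z₁₋α/₂/√(1−ρ))]. At nominal 0.05:

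| ρ | z₁₋α/₂/√(1−ρ) | True size |
|---|---|---|
| 0 | 1.960 | 0.050 |
| 0.3 | 2.343 | 0.019 |
| 0.5 | 2.772 | 0.0056 |
| 0.7 | 3.578 | 0.0003 |

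**Simulation of the named tests.** There were 3000 runs of 400 pairs with a skewed continuous outcome and a binary outcome with a baseline proportion of about 30%. ρ is the correlation of the underlying normal variables. The correlation between the resulting yes/no values is lower, so the chi-square test is less conservative than the table above at the same ρ.

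Size with no change, nominal 0.05:

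| ρ | Mann-Whitney | Signed-rank | Chi-square | McNemar |
|---|---|---|---|---|
| 0 | 0.053 | 0.051 | 0.054 | 0.053 |
| 0.5 | 0.004 | 0.045 | 0.013 | 0.045 |
| 0.7 | 0.001 | 0.048 | 0.005 | 0.051 |

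Power for a shift of 0.185 SD on the underlying scale:

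| ρ | Alpha | Mann-Whitney | Signed-rank | Chi-square | McNemar |
|---|---|---|---|---|---|
| 0.5 | 0.005 | 37% | 73% | 16% | 35% |
| 0.5 | 0.05 | 80% | 93% | 53% | 69% |
| 0.7 | 0.005 | 32% | 93% | 14% | 48% |
| 0.7 | 0.05 | 84% | 99% | 53% | 80% |

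**Pooled sample.** Take 2000 less 20% drop-out, so n = 1600, with ρ = 0.5, d = 0.185 and alpha 0.005. The power of an independent-samples z-test is Φ[(d√(n/2) − 2.807)/√(1−ρ)] = Φ[(5.233 − 2.807)/0.707] = Φ(3.43) = 0.9997. For a binary outcome moving from 40% to 46% at alpha 0.05 (underlying correlation 0.7, 4000 runs), chi-square power is 0.98 against 0.997 for McNemar. For effects of this size the pooled loss is negligible.

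**The case against.** The strongest reply is that the principal conclusion is safe. It rests on SF-12 tests that the Sample size section plans with a paired t-test, and the analysis section names that test too. This stands. SF-12 is affected only if its scores are judged non-normal and moved to the Mann-Whitney test. The effect size and alpha of 0.005 in the power comparison are also the SF-12 values. The documents tie that threshold to quality of life, and at 0.05 the loss is smaller, as the table shows. Both the loss and the conservatism depend on an assumed correlation. At the planning value of 0 the tests hold their size, although that value does not make two measurements on one person independent.

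A reader might infer more than the text supports:

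- **False claims of benefit.** With positive correlation the error goes the other way, towards missed effects. A chi-square on the T0 by T1 cross-table would test association instead of change, but nothing in the article says that this table will be used.
- **Costs sent to a rank test.** The Evaluation section assigns the economic impact to separate cost-benefit analyses, and the analysis section does not mention costs.
- **The normality rule as an error in itself.** Normally distributed variables can be shorthand for normally distributed differences in a condensed article. Preferring a mixed model or no switch at all is a choice.

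None of this rescues the two test names. The article does not leave the tests to a fuller plan; it states them. It describes no between-group comparison for which they might be meant, and the country analyses are repeats of the same tests.

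**Conclusion.** The point holds in a limited form. For non-normal variables and proportions, the stated tests do not fit a within-person comparison, and nothing else in the article corrects this. The consequence is conservatism: if the within-person correlation is 0.3 to 0.7, a nominal 0.05 test has a true size of about 0.019 down to 0.0003. In a country of about 400 participants with correlation 0.5, power roughly halves at alpha 0.005 (37% against 73% for the rank tests, 16% against 35% for proportions). At alpha 0.05 it falls by about 13 to 16 percentage points. In the pooled sample the loss is slight for effects of this size, though it could matter for smaller ones.

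These figures rest on the assumed correlation, a shift of 0.185 SD borrowed from the SF-12 planning, and the simulated outcome shapes. The direction of the error needs only that the correlation be positive. The planned SF-12 analysis and the sample size are not undermined.

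**What to change.** In the Statistical analysis plan section:

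1. Replace the Mann-Whitney U test with the Wilcoxon signed-rank test for baseline to 6-month differences in non-normal variables.
2. Replace the Pearson chi-square test with McNemar's test for binary outcomes, and with the marginal homogeneity test for outcomes with more than two categories.
3. State that the SF-12 primary comparison uses the paired t-test already assumed in the Sample size section.

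This changes two test names and adds one sentence. The tests are available in the stated software, and no new data or change to the sample size is needed.

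### The analysis section names one-way ANOVA with Bonferroni post hoc tests as the multiplicity adjustment, but this cannot adjust the paired before-after tests and does not carry over the 0.005 rule set under Sample size

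*Protocol article*

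**What the plan says.** Two sections of the Protocol article deal with multiple testing.

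**Sample size.** The primary aim is a significant difference "in the two subscales of the 12 items Short Form (SF-12") and in the five countries. The section then says: "Thus, the principal conclusion of the study will rely on 10 tests". It sets the threshold for them: "Applying the Bonferroni’s correction on the significance threshold, we will consider an alpha risk of 0.005 for the tests measuring the quality of life". The calculation uses a paired Student's t-test "with a bilateral alpha risk of 0.005, a power of 0.9".

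**Statistical analysis plan.** The before-after comparison is described first: "Differences between baseline and follow-up measurements will be assessed employing the paired T-test (for normally distributed variables"), with the Mann-Whitney U test for non-normal variables and Pearson's chi-square test for proportions. The next sentence gives the adjustment: "To adjust for multiple testing, one-way analyses of variance with post hoc testing (type Bonferroni) will be performed". Later, "the above-mentioned analyses will be repeated for each country separately". The section names no factor for the ANOVA, gives no significance level, and mentions neither the family of ten tests nor the 0.005 threshold.

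**The concern.** One-way ANOVA asks whether the means of independent groups differ. Its Bonferroni post hoc step corrects the pairwise comparisons among those groups and nothing else. The tests that carry the study's main conclusion are of another kind: each compares the same people at baseline and 6 months, within one country, on one SF-12 subscale. The procedure named as the adjustment does not act on those p-values.

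Both sections use the word Bonferroni, but for different things. Under Sample size it lowers the threshold for ten before-after hypotheses. In the analysis section it is attached to post hoc group contrasts. An analyst working only from the analysis section would find no correction that reaches the ten primary tests.

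Control of the family-wise error for the primary result is at stake. The study has no control group and its country-specific results are meant to feed policy recommendations, so a false positive in a single country would matter.

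**Working it through.** **Inputs.** From Sample size: two subscales, five countries, ten tests, two-sided alpha 0.005, power 0.9, effect size 0.185, correlation 0, 978 analysed, 20% drop-out, 1223 included, 400 per country. From Statistical analysis plan: the list of tests and the ANOVA sentence, with no alpha. An overall level of 0.05 is implied by the Bonferroni arithmetic but not written in either section.

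**1. The plan's own figures reproduce.**
- Number of tests: 2 × 5 = 10. Threshold: 0.05 / 10 = 0.005.
- Effect size: 4.3 / 23.2 = 0.185.
- Standardised change with correlation 0: 0.185 / √2 = 0.1308.
- Required number, normal approximation: ((2.807 + 1.282) / 0.1308)² ≈ 977. The noncentral t calculation gives 981. The stated 978 lies between them.
- Drop-out: 978 / 0.8 = 1222.5, rounded up to 1223.

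The Sample size section is therefore coherent on alpha: its rule is valid, and its sample size is built on that rule.

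**2. What the ANOVA would correct, by choice of factor.**
- *Country.* Five groups give 5 × 4 / 2 = 10 pairwise contrasts, each at 0.05 / 10 = 0.005. The match with the figures under Sample size is a coincidence: these hypotheses set country against country, not 6 months against baseline.
- *Time.* Two levels give a single contrast, so a post hoc test has nothing to correct. A one-way analysis would also ignore the pairing.
- *Within one country.* The analyses are to be repeated by country, and the ten primary tests are such within-country tests. Country cannot be a factor there.
- *Another subgroup, such as age or gender.* The contrasts are again between groups.

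**3. Check by simulation.** Five countries of 400 participants, with the same mean change of 0.185 standard deviations of the change score in each (3000 runs):
- ANOVA on change by country rejected in 4.5% of runs, which is its null rate.
- Paired tests at 0.005 rejected 81% of the time on average.

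The ANOVA does not detect a before-after effect shared by all countries, and it changes none of the paired p-values.

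**4. Family-wise error for the ten paired tests.**

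| Threshold per test | Dependence | Family-wise error |
|---|---|---|
| 0.005 | any | at most 10 × 0.005 = 0.05 |
| 0.005 | independent | 1 − 0.995¹⁰ = 0.049 (simulated 0.054) |
| 0.05 (assumed) | independent | 1 − 0.95¹⁰ = 0.401 (simulated 0.392) |
| 0.05 (assumed) | two subscales perfectly correlated within each country | 1 − 0.95⁵ = 0.226 |

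The simulated values come from 5000 runs. The last two rows bracket the result if 0.05 were used, because the countries are independent samples and the two subscales come from the same participants.

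**The case against.** The strongest reply is that the Sample size section already contains the decision rule. It does more than plan the size: it says which tests carry the conclusion and at what threshold the quality-of-life tests will be judged. The analysis section covers all outcomes, does not mention SF-12, and does not withdraw 0.005. Read together, the first section governs the primary family and the second adds a poorly worded device for something else. On that reading the primary error rate is controlled at about 5%.

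Much of this stands. A reader might infer that the analysis section contradicts the 0.005 alpha, or that it sets the ten tests at 0.05. The document supports neither, because that section gives no significance level. The conflict is one of procedure, not of numbers. A reader might also take 40% as the study's error rate. That figure needs three things together: the Sample size rule is disregarded, 0.05 is used instead, and the tests are independent.

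The joint reading does not rescue the sentence itself. Even with 0.005 carried over, the text presents as the adjustment for multiple testing a procedure that cannot adjust the tests described just before it. That is a stated rule that is wrong as written, not a detail left to a fuller document.

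**Conclusion.** The point holds as a misdescribed multiplicity device that is inconsistent with the Sample size section. That the ANOVA cannot adjust the paired tests is certain and does not depend on which factor was meant.

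The consequence is conditional: about 5% family-wise error if 0.005 is applied to the ten tests; between about 23% and 40% if the analysis section were followed alone and 0.05 were used, depending on how strongly the two subscales are correlated.

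The point does not extend to what counts as overall success. A reader might infer from the Bonferroni step that one significant test out of ten is enough, or from the wording of the aim that all ten are needed. The article does not settle this, and the choice is the sponsor's. Correcting the sentence is worthwhile because it removes the risk of an uncorrected primary analysis at almost no cost.

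**What to change.** In the Statistical analysis plan section:

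1. Delete the ANOVA sentence as a statement about adjustment for multiple testing.
2. State that the ten primary paired SF-12 tests (two subscales in five countries) are each judged at a two-sided alpha of 0.005. Holm's step-down procedure over the ten tests at an overall 0.05 is a valid alternative and is never less powerful, but it is not needed to repair the defect.
3. Keep ANOVA with Bonferroni post hoc tests only for comparing change scores between groups, say so, and name the factor, for example country.

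The cost is a few lines of text. The sample-size calculation already uses 0.005, so its result does not change, and no new data are needed.

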## Methods and analysis

### Methodology

The methodology used for the community-based intervention of EFFICHRONIC is the ‘chronic disease self-management programme’ developed at Stanford University. The CDSMP is a public health intervention provided by trained monitors. The programme is strongly evidence-based and consists of the following conceptual elements: self-efficacy, empowerment, salutogenesis, peer-to-peer education and vicarious training. It includes action planning and feedback about problem-solving skills and other competencies such as the reinterpretation of symptoms and training in disease management.

A cascade training model is used in the CDSMP method. On top are Self-Management Resource Centre licensed T-trainers possessing the maximum teaching expertise. They are in charge of training master trainers, who in their turn train monitors (or leaders) who will conduct the chronic disease self-management workshops. The monitors receive practical training on the philosophical and methodological basis of the CDSMP: empowerment, self-efficacy, group management, management of painful emotions, positive health and efficient communication among other skills. Once trained, the monitors facilitate the workshops in pairs. In each country, minimum 32 monitors will be trained to instruct the end-users: people with chronic conditions or caregivers. The CDSMP workshops last for 6 weeks with sessions of 2.5 hours once a week in groups of 12–20 participants. The programme fidelity and quality plan includes the supervision of workshops in the community by the master trainers through periodic protocolled monitor audits. Workshop assistants receive a handout with the workshop topics and homework assignments, a consultation book and a certificate of attendance if they were present at minimum 4 of the 6 sessions.

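### The ten principal paired t-tests treat workshop members as independent; if changes correlate within workshops, each test's error rate exceeds the planned 0.005

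*Protocol article*

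**What the plan says.** The Methodology section of the Protocol article describes weekly "sessions of 2.5 hours once a week in groups of 12–20 participants" over six weeks. It names learning from peers among the elements of the programme and adds: "Once trained, the monitors facilitate the workshops in pairs". The Implementation section says that "between 100 and 140 workshops (20–28 per country) will have to be conducted".

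The Sample size section bases the principal conclusion on ten tests. The section names two SF-12 subscales and five countries, so these are naturally read as two subscales in each country. Bonferroni correction gives 0.005 per test. The calculation is made "by a paired Student’s t-test, with a bilateral alpha risk of 0.005", with power 0.9 and a baseline-to-6-month correlation of 0. It arrives at 978 people to analyse and 1223 to include.

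The Statistical analysis plan section repeats the paired t-test for normally distributed outcomes. It says that the relationship between a 6-month outcome and explanatory variables "will be determined using ordinary least squares regression analysis", and that the analyses are repeated in each country. Neither section mentions a workshop effect, a cluster-robust variance, an ICC or a design effect.

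**The concern.** A paired t-test on individuals takes the standard error of the mean change from the spread of individual changes divided by the square root of the number of people. That is right only if one person's change says nothing about another's. Here people go through the programme in the same small group, with the same two monitors, and the group is part of how it is meant to work. A good group or a good pair of monitors can move all its members together, and pairing each person with their own baseline does not remove this.

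The Bonferroni argument needs each of the ten tests to hold 0.005. If the standard errors are too small, the per-test error is higher and the family-wise error passes 5%. The country-level tests matter most: they carry the principal conclusion, each rests on only 20 to 28 workshops, and the section on guidelines and policy recommendations builds on country-specific results.

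**Working it through.** **Inputs from the Protocol article.** Effect size: "The lowest Cohen’s d is therefore of 0.185 in quality of life domains" (4.3/23.2 = 0.1853). Two-sided alpha 0.005, power 0.90, correlation 0, drop-out 20%, 400 per country, 2000 in all, 12 to 20 people per workshop, 20 to 28 workshops per country.

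**Assumed.** ICC of the change score 0.01, 0.02 or 0.05, as the article gives none. Workshop size m = 16, the middle of 12 to 20; the planned totals imply 2000/140 = 14.3 to 2000/100 = 20.

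**Step 1: reproduce the plan's figure.** With correlation 0 the variance of the difference is twice the single-time variance, so n = 2 × ((2.807 + 1.282)/0.185)² = 977. The exact noncentral t calculation gives 978 with d = 4.3/23.2 and 981 with d = 0.185. Then 978/0.8 = 1223. The stated figures are recovered with a design effect of 1, so they contain no hidden allowance for grouping.

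**Step 2: apply a design effect.** DE = 1 + (m − 1) × ICC. The naive standard error is too small by a factor √DE, so the true alpha is 2 × (1 − Φ(2.807/√DE)). Family-wise error over ten independent tests is 1 − (1 − alpha)^10.

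| | no clustering | ICC 0.01 | ICC 0.02 | ICC 0.05 |
|---|---|---|---|---|
| DE at m = 16 | 1.00 | 1.15 | 1.30 | 1.75 |
| true alpha at nominal 0.005 | 0.005 | 0.009 | 0.014 | 0.034 |
| family-wise error, ten tests | 5% | 9% | 13% | 29% |
| effective size of 400 (400/DE) | 400 | 348 | 308 | 229 |
| 978 × DE | 978 | 1125 | 1271 | 1712 |

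Over m = 12 to 20 and the same ICCs, DE runs from 1.11 to 1.95 and the true alpha from about 0.008 to 0.044. The family-wise row treats the ten tests as independent; two subscales in the same people are not, so it is approximate.

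**Step 3: power.** Pooled, 2000/978 = 2.04, so 2000 analysed carries a design effect up to about 2.04 even at correlation 0. That is an ICC of about 0.095 at m = 12, 0.070 at m = 16 and 0.055 at m = 20. At m = 20 and ICC 0.05, pooled power is still 0.915. If 2000 were the number enrolled and 1600 the number analysed, the limit would be 1600/978 = 1.64.

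Per country, under the plan's own inputs, 400 analysed gives power of 0.42 without clustering and 0.35, 0.30 and 0.20 at the three ICCs with m = 16.

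**The case against.** **The inflation is conditional.** A reader might infer that the p-values are certainly too small. The documents do not support that, because they report no ICC. Shared recruitment channels and calendar periods mainly produce shared baseline levels, and stable level differences cancel in a within-person change. The peer group and the monitors are the relevant sources. This stands: the direction is certain only for a positive ICC of the change, and the size depends on its value.

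**The 978 and power.** A reader might infer that the study is too small. A correlation of 0 is a cautious choice. The required number scales as 978 × (1 − r) × DE, so design effects of 1.15, 1.30 and 1.75 are absorbed within 978 once r reaches about 0.13, 0.23 and 0.43. The true r is not given either. The Study population section also aims at 2000 people who are evaluated, from at least 2500 recruited. The pooled power worry therefore falls away. The low per-country power is mostly the gap between 400 and 978; clustering makes it worse but does not cause it.

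**The regression.** A reader might infer that every ordinary least squares interval is too narrow. That holds for covariates that are constant or correlated within workshops. For covariates that vary mainly within workshops the bias may be small or reversed. The 0.005 threshold belongs to the pre-post tests, not to the regression.

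**Country.** The lack of a named country term might look like part of the same fault. It is not: the ten tests are run by country, and in a pooled paired test with countries as fixed strata, differences between countries in mean change enlarge the standard deviation, which makes the test conservative.

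None of this answers the main point. Ample pooled numbers do not correct a type I error rate, and repeating the analysis by country leaves workshop grouping inside each country.

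**Conclusion.** The concern holds for the ten principal pre-post tests, conditionally on correlated change within workshops. Such correlation is plausible for a peer-group programme led by shared monitors, and the stated methods make no allowance for it. On the assumed ICCs of 0.01 to 0.05 and 16 people per workshop, a nominal 0.005 becomes about two to seven times as large, and precision per country is that of 348 down to 229 independent people. Confidence is high that independence is assumed, since the sample size reproduces with no design effect and the tests are named outright. It is moderate on the size, which rests on an ICC that the documents do not give. This should be corrected: it concerns type I error and per-country precision, not pooled power.

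**What to change.** Keep the workshop identifier in the anonymised central dataset; nothing in the article says that it will be dropped, but without it the correction cannot be made later. In each country, analyse the within-person change in a linear mixed model with a random effect for workshop, or use workshop-clustered standard errors with a small-sample correction, since there are only 20 to 28 workshops per country. Do the same in the pooled analysis, with country as a fixed effect, and in the regression. State the assumed ICC and design effect beside 978, with the remark that the pooled 2000 covers a design effect up to about 2.04.

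The cost is a different model call in the same software, slightly more analysis work and somewhat wider confidence intervals. No extra participants, visits or changes to delivery are needed.
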